## **16.6 Two week post-treatment visit (RDT-positive women treated with DHA-PQ only)**

Women treated with DHA-PQ will be asked to return to the clinic 14 days after the first dose is given. A venous blood sample will be taken for testing of blood DHA-PQ levels, full blood count (red blood cell count, white blood cell count, differential blood cell count); blood haemoglobin levels; and biochemistry (bilirubin, alanine aminotransferase and creatine) for later analysis.

## **16.7 Unscheduled visits during pregnancy**

Participants will be encouraged to visit the clinic if they feel unwell between scheduled appointments.

Participants who present between appointments will be examined by study staff. Presenting symptoms, axillary temperature and blood pressure will be recorded. A finger-prick blood sample will be taken for Hb measurement and malaria RDT and thick and thin microscopy smears. Women presenting with serious adverse events possibly associated with DHA-PQ will have a 2 ml venous blood sample taken to measure blood drug levels. Any illness will be treated as appropriate and according to standard local care. The date of attendance, diagnosis and treatment will be recorded on the CRF, and any adverse events reported according to standard procedures.

## **16.8 Delivery visit**

Women will be encouraged to deliver on the maternity wards of the participating clinics, in which case they will be assisted to delivery by regular clinic midwives, and a specially trained member of the study team will visit them on the ward and perform relevant examinations shortly after delivery. Women who deliver at home will be identified using a network of community nurses and traditional birth attendants, and will be visited by a member of the study staff within 48 hours, to collect, as far as possible, the same information.

### **16.8.1 Peripheral blood sampling**

A 5 ml venous blood sample will be taken from the mother and tested for malaria using RDT, standard microscopy and PCR; and tested for Hb concentration using hemocue. Women found to have malaria infection by RDT or microscopy, or anaemia ( $\text{Hb} \leq 11 \text{ g/L}$ ) will be treated as appropriate. This sample will also be used to test for markers for general and pregnancy-specific immunity to malaria, and for markers of SP resistance and iron deficiency.

### **16.8.2 Placental sampling**

A blood sample will be collected from the delivered placenta by making an incision on the maternal side and collecting the pooled blood. This sample will be tested for malaria using RDT, standard microscopy of blood smear and PCR.

A 2cm x 2cm x 1cm specimen of placental tissue will be taken from the maternal side for histopathology testing for current and past malarial infection.

#### **16.8.3 Umbilical cord sampling**

An umbilical cord blood sample will be taken and tested for Hb and malaria using RDT, standard microscopy of blood smear and PCR. If the RDT is positive for malaria, microscopy will be prioritised for within the next 24 hours and if positive by microscopy the baby will be referred to the hospital for treatment of malaria.

#### **16.8.4 Examination of the baby**

The baby will be weighed using accurate digital scales, and will be examined for vital status, presence of any significant congenital anomalies, and gestational age at birth using the Ballard's score. After 24 hours, the baby will be re-examined for the presence of jaundice. Examinations will be done by specially trained study nurses or by the study physician.

### **16.9 Seven-day postnatal visit**

Participants and their babies will be seen at the clinic by a study physician around seven days after birth, if possible to correspond with the baby's first vaccination visit. The baby will be examined for the presence of jaundice and for any congenital anomalies that may have been missed at delivery. Babies with symptoms of malaria will have blood samples taken for testing by RDT, microscopy and PCR; treatment will be provided based on the RDT results. Standard postnatal advice and healthcare will be provided as needed for mother and baby, and any treatment and clinical findings for the baby recorded on the CRF. Routine postnatal care will be provided for the women. Women who do not attend for this appointment will be visited at home if possible. Any infant deaths occurring before the visit will be recorded; the date and probable cause of death will be ascertained by verbal autopsy.

### **16.10 Six-week postnatal visit**

Participants and their babies will be seen again at the clinic by a study physician around six to eight weeks after birth, at their baby's second vaccination visit. The baby will be examined for the presence of congenital anomalies that may have been missed at delivery or the first visit. Babies with symptoms of malaria will have heel-prick blood samples taken for testing by RDT, microscopy and PCR; treatment will be provided based on the RDT results. Standard postnatal advice and healthcare will be provided as needed for mother and baby, and any treatment and clinical findings for the baby recorded on the CRF. Women who do not attend the scheduled appointment will be visited at home if possible. Any infant deaths occurring before the visit will be recorded; the date and probable cause of death will be ascertained by verbal autopsy. Participants will also be asked about their use of healthcare for the baby since birth.

## 16.11 Unscheduled postnatal visits

Women will be encouraged to attend the clinic if their baby becomes unwell during the follow-up period. Babies will be examined by study staff. Presenting symptoms, axillary temperature and blood pressure will be recorded. A heel-prick blood sample will be taken for Hb measurement and malaria RDT and thick and thin microscopy smears. Any illness will be treated as appropriate and according to standard local care. The date of attendance, diagnosis and treatment will be recorded on the CRF, and any adverse events reported according to standard procedures. Clinical care will also be provided for women who attend because of their own illness, but this will not be recorded as part of the study.

## 16.12 Follow-up of non-attenders

Participants who do not attend scheduled appointments will be contacted by a member of study staff by telephone, if the participant has provided a contact telephone number. If participants cannot be contacted by telephone, or if they still do not attend when reminded, they will be visited at home within two weeks of the missed appointment by community-based Health Surveillance Assistants and invited to re-attend, or if they no longer wish to participate in the trial their reasons recorded.

## 16.13 Data collection methods for economics and implementability sub-studies

Health facility costs and intervention costs will be collected through observational studies, key informant interviews and sight of relevant financial documents. The following cost data will be collected:

- Materials and drugs: SP, DHA-PQ, diagnostic tests, treatment of pregnant women with symptomatic malaria, treatment of maternal anaemia, treatment of infant anaemia and treatment for low birth weight infants. It may be necessary to collect treatment costs outside of the trial facility, so that the costs of 'actual practice' rather than 'trial practice' can be estimated. Cost data will be collected through review of accounting documents and interviews with key informants drawn from facility management (e.g. accountant, health facility in-charge, department managers).
- Staff time: The interventions will be provided within the antenatal care programme of the Ministry of Health of Malawi. The incremental staff time of the two interventions will be estimated through a combination of interviews with health workers and observation.

**Out of pocket costs associated with pregnancy care and with the prevention and treatment of malaria during pregnancy will be estimated using exit surveys at antenatal care clinics (ANCs). Women will be asked about how many times they have attended the ANC during their current pregnancy and about health tests, care and medical attention they have received. They will be asked about malaria prevention tools they may have been given at the ANC or that they may have bought or received somewhere else. They will be asked about health related costs incurred during their current pregnancy. In order to be able to estimate their social status, women will be**

asked about their family, occupation, sources of income, their houses and assets owned.

In order to allow comparison, we propose to include both women who experienced at least one episode of malaria and women who did not experience any episode of malaria during their current pregnancy in the study. Only those women who will sign informed content forms will be administered the questionnaire and included in the study. The participant information sheet and consent form are presented in Appendix 3. 385 pregnant women who experienced malaria and 385 pregnant women who did not experience malaria will be interviewed.

Costs of caring for low birth weight infants will be collected in health assessments six to eight weeks after delivery.

Contextual information will be collected using focus group discussions (FGDs), community in-depth interviews and stakeholder interviews.

Acceptability will be studied using FGDs, semi-structured interviews, in-depth interviews, observations and a discrete choice experiment.

Feasibility and implementability will be explored using survey techniques, FGDs, semi-structured interviews and in depth-interviews.

## 17 Statistical methods

### 17.1 Sample size

The trial will use a stratified design with one strata for primigravidae and secundigravidae and one strata for multigravidae. It is designed to detect a 25% reduction (RR 0.75) in composite adverse birth outcomes (SGA, low birth weight and pre-term birth) in women in their first and second pregnancies with an 90% power and a 2-sided significance level of 0.05, if the rate of placental malaria in the IPT-SP group is similar to that found ongoing observational studies of women receiving routine care in the same area of Malawi. The proposed difference is based on four previous trials of IPTp which jointly reduced low birth weight by 29%. Thus the efficacy of ISTp is expected to be similar to the efficacy of IPTp before the emergence of widespread SP resistance. In the ongoing IPT-mon study in Malawi, the incidence of SGA, low birth weight or preterm birth was 40.3% (N=494) ([name], personal communication). Therefore the study is designed to detect a 25% difference between 40.3% in the control (IPTp) group and 30.2% in the intervention (ISTp) group.

This would require 491 participants in each arm or 982 in total. To allow for a 15% loss to follow-up, 1155 women in their first and second pregnancies will be recruited. This sample size would also have an 81% power to detect a 25% or greater reduction in placental malaria (active or past infection), with a significance level of 0.05. If a power of 80% is used, the study can detect a difference of 21.8% or greater in the primary endpoint. If the incidence is 33.3% instead of 40.3% the study still has 80% power (instead of 90%) to detect a 25% reduction.

The trial is also designed to detect a 50% reduction in past or present placental malaria infection at delivery in multigravidae, based on previous studies of IPTp, assessed by placental histopathology and RDT. The current rate in women in Malawi who are taking IPTp-SP is estimated from IPT-mon at 20.5% ([name], personal communication). A reduction by 50% to 10.25% will require 213 women per arm or 426 in total. To allow for a 15% loss to follow-up we will recruit 500 multigravidae.

The total sample size will therefore be  $1155 + 500 = 1655$ .

## 17.2 Randomization

Two randomization sequences will be computer-generated by the study statistician at Liverpool School of Tropical Medicine, one for women in their first and second pregnancies and another for multigravidae. The method used for each will be block randomization, stratified by study site to ensure an equal proportion of participants in each intervention group from each site. The length of each block will vary and will ensure that allocation concealment is fully maintained and allocation well distributed over the seasons. The allocation ratio for the two study arms will be 1:1.

Recruitment will be 'competitive' between study sites, meaning that the number of participants recruited at each site may differ depending on the respective rates of enrolment. A sufficient number of randomization codes will be generated for each site to allow for this.

The randomization sequences will be sent to the study sites in Malawi and local investigators will prepare opaque envelopes, numbered sequentially, with the allocated group code and details for that number inside. For each newly enrolled participant, an envelope from the correct sequence (according to gravidity group) will be opened sequentially to identify the group that they are allocated to, thus concealing the upcoming allocation from the participants, clinic staff and study staff. The number on the envelope represents the study number allocated to that participant and will become their unique identifier in the trial. This number will be recorded with their screening registration number on their CRF, and the participants provided with a trial identity card confirming their study number. Once a study number has been assigned to a participant it will not be used again, for example if a participant discontinues. If a study number is allocated incorrectly, it will not be reassigned and randomization will continue with the next sequential number.

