## 7 Trial design

### 7.1 Overview of design

This will be a two-arm randomized controlled trial conducted at three or more sites in southern Malawi with high levels of SP resistance and high ITN coverage. Enrolment will be stratified by gravidity group (stratified design); one for primi and secundigravidae (G1+2) and one for multigravidae (G3+). The study requires 1665 women overall, including 1155 primi and secundigravidae and 500 multigravidae. It is designed to detect at least a 25% reduction in the primary endpoint consisting of a composite of small-for-gestational age (SGA), low birth weight or preterm birth in women in their first or second pregnancies, and at least a 50% decrease in placental malaria in women in multigravidae. The study will be open label as it will not be possible to blind the participants to their allocation, although where possible laboratory staff undertaking trial-related diagnostic tests will be blinded.

Antenatal clinic sites at Mpemba, Madziabango and Zingwangwa and Chileka will be involved. If less than half the required number of participants is recruited within the first half of the recruitment period, antenatal sites in neighbouring clinics in Blantyre, Zomba or Chikawa districts may be added.

Participants will be HIV-negative pregnant women. They will be screened for eligibility and given information about the study at their first contact with antenatal services before 28 weeks gestation and will be enrolled at 16 to 28 weeks gestation. The study is expected to start in the fourth quarter of 2010 or first quarter of 2011 and recruit for a period of 18 to 30 months, with a further six months follow-up.

Participants will be randomly allocated (see section 17.2 for description of the randomization process) to receive either at least three doses of IPTp with SP or at least three scheduled screenings with an RDT and treatment with DHA-PQ if they are RDT-positive. All participants will be given an insecticide-treated bed net if they do not already have one.

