### 7.2.3 Open label design

Participants will be informed of the intervention they are assigned to, since the processes for IPTp and ISTp are different, and blinding is not therefore possible. Blinding will be undertaken only for diagnostic tests performed by laboratory personnel.

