## 10 Screening and eligibility assessment

Potential participants will be screened for eligibility when attending their first routine antenatal appointment. If they meet the inclusion criteria they will be offered enrolment following informed consent. Women who do not meet the inclusion criteria, or who do not wish to participate in the trial, will receive usual antenatal care, including the standard IPTp-SP schedule.

Eligibility screening will be conducted by clinic nurses and midwives and supported by study staff. Screening data will be recorded in a log that will be kept in the investigators site file. One screening log will be kept per site. This record will be used to report how many women attended for antenatal appointments, how many were potentially eligible, how many were enrolled into the study, and reasons for non-eligibility of those not enrolled. It will be used to ensure that women are selected for the study without bias. Each screened woman will be assigned a screening registration number in sequential order by the study clinic. Screened attendees who do not meet the eligibility criteria for the trial will be considered screening failures, in which case the registration number will not be re-used; however the woman can re-enter the study at a later date if she meets the eligibility criteria at that visit.

Gestational age will initially be estimated first using a combination of fundal height as measured by the midwife and last menstrual period (LMP) dates provided by the woman, where available. Women attending antenatal care for the first time after 28 weeks gestation will be excluded from the trial. Women attending before 16 weeks gestation will be screened for inclusion, given information about the trial and enrolled when they next attend between 16 and 28 weeks gestation. Women who are eligible and express an interest in the trial may receive an ultrasound scan at this point, using portable equipment to accurately assess the gestational age of the pregnancy and identify multiple gestations. Alternatively the scan may be done at another appointment shortly after enrolment. The ultrasound scan will be done by a trained clinician who is part of the study team. Any women identified as having multiple gestations will be excluded from the study. Ultrasound scans are not part of routine antenatal care in Malawi; the equipment will be specially purchased and study staff trained to use it.

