#### 16.1.1 Enrolment

After informed consent has been signed, participants will be randomly allocated (see section 17.2) to receive either IPTp or ISTp (see section 15.1) and issued with a trial identity card with their unique study identification number. Participants will be informed of study intervention they have been allocated to.

At this stage study staff will ask the participant for a home or mobile telephone number if they have one, and home address or a description of the location of their home, and for their verbal consent to be visited at home two days after receiving the study drugs (if they receive DHA-PQ) and whenever they do not attend scheduled appointments.

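### Local investigators pack the allocation envelopes from lists sent to the sites, so concealment fails for the packers and is not assured for those who screen and enrol

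*Combined protocol and SAP*

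**What the plan says.** Section 17.2 starts with an off-site step: "Two randomization sequences will be computer-generated by the study statistician at Liverpool School of Tropical Medicine". There is one sequence for first and second pregnancies and one for multigravidae, each blocked and stratified by site. The next step moves the lists to the field: "The randomization sequences will be sent to the study sites in Malawi and local investigators will prepare opaque envelopes, numbered sequentially". Each envelope holds the group for its number, and that number becomes the participant's study identifier. Envelopes are opened in order within the gravidity group, which the plan describes as "thus concealing the upcoming allocation from the participants, clinic staff and study staff". On blocks it says: "The length of each block will vary and will ensure that allocation concealment is fully maintained".

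Three other sections bear on the point.
- **Blinding.** Section 7.1 says "The study will be open label as it will not be possible to blind the participants to their allocation", and section 7.2.3 says "Blinding will be undertaken only for diagnostic tests performed by laboratory personnel".
- **Screening.** Section 10 says "Eligibility screening will be conducted by clinic nurses and midwives and supported by study staff".
- **Order of events.** Section 16.1.1 says "After informed consent has been signed, participants will be randomly allocated".

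**The concern.** Concealment protects against selection bias only if nobody who can influence which woman is enrolled, or when, knows the next allocation. Section 17.2 puts the full sequence in the hands of trial personnel at the recruiting sites and then states that study staff are kept unaware of it. Both statements cannot be true of the people who do the packing.

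The plan leaves room to act on such knowledge. Initial gestational age, which decides eligibility, rests on fundal height and reported last menstrual period (sections 8.1 and 10). A woman who fails screening may come back and be enrolled later (section 10). A study number allocated in error is passed over and the next one used (section 17.2), and no audit of such numbers is described.

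If women with a higher risk of an adverse birth outcome were directed to one arm, the comparison would be biased. No analysis could fully repair this, because the baseline description in section 17.3.2 reveals only measured imbalance.

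**Working it through.** **Step 1. Who knows the sequence.** These are the stages in section 17.2, with what the plan does and does not state.

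| Stage | Stated | Not stated |
|---|---|---|
| Generation | Statistician, off site | – |
| Transfer | Sequences sent to the sites | Who receives and keeps them |
| Packing | Local investigators; opaque, numbered envelopes | That envelopes are sealed or tamper-evident; that packers have no part in recruitment |
| After packing | Nothing | Whether the list is destroyed, returned or locked away |
| Opening | In sequence, by gravidity group | Any record on the envelope before opening; any audit of envelope use |

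A packer necessarily sees the group attached to each number. For that person the concealment claim fails by construction.

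**Step 2. Are packers separate from recruitment?** No section says so. Section 20.3 lists the principal investigator and co-investigators among those who may prescribe study drug, so investigators are not shown to be remote from participants. Section 10 has study staff supporting eligibility screening. Overlap is possible but is not stated.

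**Step 3. Do varying blocks repair it?** In an open-label trial, staff learn each allocation once it is made and may guess the end of a block. Varying the block length hinders that guess. It does nothing against a person who has read the sequence.

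**Step 4. The plan's own sample size.** Section 17.1 gives 40.3% against a 25% relative reduction, two-sided alpha 0.05, 90% power and 491 per arm. With p1 = 0.403, p2 = 0.75 × 0.403 = 0.30225, d = 0.10075 and mean 0.352625:

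- n0 = [1.960 × √(2 × 0.352625 × 0.647375) + 1.2816 × √(0.403 × 0.597 + 0.30225 × 0.69775)]² / d² ≈ 470.5, or 471 rounded up
- with continuity correction, n = (n0/4) × [1 + √(1 + 4/(n0 × d))]² ≈ 490.2, or 491 rounded up

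The stated 491 is reproduced. Nothing in the present point alters it.

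**Step 5. Illustrative size.** The documents give no steering rate, so the two inputs here are assumptions: s, the share of enrolments steered, and c, the difference in adverse-outcome risk between women steered to one arm and women steered to the other. All steering is taken to favour the same arm, and there is no treatment effect.

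- Bias: b = s × c
- SE of the difference at the control rate: √(2 × 0.403 × 0.597 / 491) = 0.0313
- Two-sided type I error: Φ(−1.96 − b/SE) + Φ(−1.96 + b/SE)

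| s | c (points) | b (points) | b/SE | Type I error |
|---|---|---|---|---|
| 2% | 10 | 0.2 | 0.064 | 5.0% |
| 5% | 10 | 0.5 | 0.160 | 5.3% |
| 5% | 20 | 1.0 | 0.319 | 6.2% |
| 10% | 20 | 2.0 | 0.639 | 9.8% |

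Against the target difference of 40.3 − 30.2 = 10.1 points, a bias of 1 point is about 10% and a bias of 2 points about 20%.

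**The case against.** The strongest reply is that the plan has several protections and that nothing shows a recruiter knowing the next allocation. Clinic nurses and midwives lead screening. Consent is signed before allocation. Envelopes are opaque and opened in order. Section 10 requires one screening log per site, with sequential registration numbers and recorded reasons for non-eligibility, expressly to guard against biased selection. Section 17.2 links the study number to the screening number on the case record form, and section 19 provides monitoring on the sponsor's behalf.

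Much of this stands, and it limits what can be said. A reader might infer that allocation is known to the staff who enrol women, or that the list stays on site throughout recruitment. The documents support neither reading. They do not say that packers also screen, consent or enrol, and they say only that the sequences are sent, not that they are kept. A reader might also take 9.8% as the expected error rate. It is the top of an assumed range, and steering in both directions would shrink the net bias towards zero.

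What the reply does not do is restore the concealment claim. The log and the number link make a deferred or skipped woman partly traceable afterwards. They do not stop a person who has seen the list from influencing who is enrolled and when.

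**Conclusion.** The point holds in a limited form. The plan's statement that upcoming allocation is hidden from study staff is untrue for the investigators who pack the envelopes. For those who screen and enrol it is not assured, rather than shown to be broken, because role separation, sealing and custody of the list are all left unstated. This conclusion rests on the text of section 17.2 and on the absence of any repairing statement elsewhere; it needs no figure. The range of about 5.0% to 9.8% for type I error is an illustration for the first-and-second-pregnancy stratum under assumed, one-directional steering, not an estimate. The procedure should be changed before recruitment, since lost concealment cannot be recovered at analysis.

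**What to change.** Replace the packing step in section 17.2 with wording such as: *The statistician's office at the sponsor, which generates the sequences, packs and seals the opaque envelopes by site and gravidity stratum and ships them sealed. No list is held by anyone who recruits, treats or assesses participants. Before an envelope is opened, the participant's screening number and the date are written on it.*

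If packing has to be done locally, name a person with none of those three roles and require that person to return or destroy the list afterwards. The trial's own monitor should not be that person, because it would then be checking its own work.

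Delete the statement that varying block length ensures full concealment, or limit it to guarding against prediction from past allocations.

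The cost is courier charges and some packing time, with no additional staff. The main drawback is restocking lead time: recruitment is competitive and lists are site-specific, so a fast site could run short unless surplus envelopes are shipped at the outset. Sample size, power and alpha do not change.
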